# Effects of prophylactic swallowing exercises on dysphagia and quality of life in patients with head and neck cancer receiving (chemo) radiotherapy: the Redyor study, a protocol for a randomized clinical trial

**DOI:** 10.1186/s13063-019-3587-x

**Published:** 2019-08-14

**Keywords:** Deglutition, Deglutition disorders, Head and neck cancer patients, Rehabilitation, EAT 10

## Abstract

**Background:**

Radiation-induced dysphagia is common in patients with head and neck cancer (HNC). Available evidence suggests that exercise therapy prior to oncological treatment could potentially improve deglutition and quality of life; however, a randomized clinical trial is needed to confirm this observation.

**Methods/design:**

The Redyor study is a single-blind randomized clinical trial designed to compare the effect of prophylactic oropharyngeal exercises on quality of life and dysphagia of 52 patients with HNC referred to the Radiotherapy Department. The intervention will consist of respiratory muscle training (3 times/day, 5 days/week, 21 weeks) added to the standard swallow therapy. All patients will perform the same exercise intervention, but at different times: before chemoradiotherapy (CRT; early intervention group) or immediately after completing CRT (late intervention group). The main outcome will be change in dysphagia severity assessed with the Penetration-Aspiration Scale in videofluoroscopy study; quality of life will be assessed with the EORTC-QLQ-C30 and its Head and Neck Cancer Module (QLQ-H&N35) at 3, 6, and 12 months after completing CRT.

**Discussion:**

This ongoing clinical trial, registered in 2016, is based on the hypothesis that undergoing a pre-radiotherapy rehabilitation (pre-habilitation) program will have greater benefits (less decrease in quality of life, less delay in swallowing parameters, and less severe dysphagia) compared to post-CRT rehabilitation. The main objective is to assess dysphagia severity in HNC patients; and secondly, to evaluate changes in dysphagia-related quality of life, and to determine the correlation between a clinical variable and instrumental parameters during this period.

**Trial registration:**

NCT0209009911.

**Electronic supplementary material:**

The online version of this article (10.1186/s13063-019-3587-x) contains supplementary material, which is available to authorized users.

## Background

Squamous head and neck cancer (HNC) has high incidence in developed countries. HNC is categorized according to the area of the head or neck in which it occurs, with greater incidence in the larynx, followed by the oropharynx, oral cavity, and hypopharynx. At the time of diagnosis, 1% of all patients have a distant metastasis, with the highest rate (4%) observed in the nasopharynx and earlier-stage tumors located in the larynx and the oral cavity. Tobacco and alcohol use and human papilloma virus (HPV) infection are the most important risk factors [1].

Although chemo-radiation therapy (CRT) protocols have been designed to preserve swallowing function and essential speech organs, dysphagia is a frequent symptom in these patients and the primary adverse effects are usually associated with acute or late swallowing disturbances [2–6]. Preservation of underlying anatomical structures does not guarantee normal function. CRT affects target areas and may result in lack of coordination of swallowing phases, lack of swallow coordination with respiratory function, reduced elevation of larynx, delayed laryngeal closure, loss of tongue strength, and prolonged oral and pharyngeal time in swallowing [6–9]. Radiation-induced dysphagia pathogenesis includes an initial process of acute inflammation with the appearance of edema, which may be followed by fibrosis of the soft tissues resulting in neurological alteration and muscle damage. Xerostomia, pain, and pharynx obliteration are the key elements of acute-phase dysphagia. At 3 months, many patients have regained swallowing function. In later stages, with the appearance of diffuse fibrosis of the connective tissue and skin in the irradiated area, changes are observed in the efficacy and safety of swallowing. It is believed that hypoxia and chronic oxidative stress could perpetuate tissue damage even long after the end of treatment, which would explain the appearance of dysphagia in the chronic phase [10]. These side effects contribute to higher rates of malnourishment, weight loss, and bronchoaspiration [6, 11], resulting in a need for alternative or supplementary methods for feeding and hydration, both early and long-term [8].

For years, delays have been reported in referring HNC patients undergoing CRT to rehabilitation departments. Patients were only referred when they presented with obvious swallow deficits or the consequent malnourishment, weight loss, changes in voice characteristics, etc., often months or years post-CRT [12]. The greater the delay, the worse is the patient’s detrimental muscle disuse and swallow dysfunction [13, 14].

In recent years, there has been a growing interest in swallowing interventions. Potential benefits of prophylactic exercises conducted during [15–17], soon after [18], or before the CRT intervention [19] have been described, and improvements in functional swallow outcomes and quality of life parameters after respiratory therapy (RT) intervention have been reported [14]. Nevertheless, supportive care for earlier dysphagia management in rehabilitation departments continues to play a secondary role in HNC diagnosis in most health systems [9, 12].

New ways to treat HNC dysphagia in an early intervention are now being explored, using inspiratory and expiratory muscle training (IEMT), a technique initially developed for patients with chronic respiratory diseases [20] that has shown its usefulness in patients with dysphagia [21–25]. Designed to improve respiratory muscle strength, IEMT also trains muscles involved in coughing, speech, and swallowing [26]. The hypothesis of the ongoing Redyor (Rehabilitation Dysphagia Oropharyngeal Cancer) study is that improvement of the swallowing function is due to the strengthening of the suprahyoid muscle (anterior portion of the digastric, mylohyoid, and geniohyoid). The suprahyoid/submental muscles participate in the pharyngeal phase of swallowing. Their weakness or lack of coordination can decrease the amplitude of the hyoid, causing an inadequate opening of the upper esophageal sphincter that exposes the airway to the passage of the bolus. Some authors have evaluated the effect of IEMT on the swallow muscles by videofluoroscopy swallow studies (VFSS), noting that the amplitude of the hyoid movements increase during training, both in the oral (jaw and tongue) and pharyngeal phases [27]. The usefulness of IEMT to train respiratory, cough, speech, and swallowing muscles is well established in pathologies other than chronic obstructive pulmonary disease, such as stroke-related dysphagia [28], but the most recent neurophysiological findings suggest the capacity for improving motor recruitment of the suprahyoid musculature, the activity of pharyngeal musculature, and the palate, as well as an increase in the amplitude of the movements of the hyoid [29, 30], could be considered and included as a new therapeutic tool for the treatment of HNC swallowing disturbances in the acute stage after diagnosis.

Available data suggest that pre-habilitation exercises could further improve these results [18, 19]. The Redyor study is based on the hypothesis that an early intervention could contribute to preserve swallow function and quality of life. The main objective of this study is to determine the effectiveness of 21-week IEMT added to standard swallowing exercises performed before or immediately after CRT (early or late intervention, respectively) to preserve swallow function in patients with HNC receiving radiotherapy in a randomized clinical trial. Secondary objectives of this study include assessing changes in quality of life, comparing the effectiveness of the VFSS and Volume-Viscosity Swallow Test (V-VST) for screening dysphagia, and evaluating the effect of IEMT added to standard swallow exercises in a home-based dysphagia rehabilitation program in patients with HNC undergoing CRT.

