### Outcome measures

Main outcome variable:
Change in dysphagia severity observed by VFSS and assessed with the Penetration-Aspiration Scale: scores 1–2 indicate normal swallowing, 3–5 penetration, and ≥ 6 aspiration

Secondary outcome variables:
Change in quality of life, assessed with the European Organization of Research and Treatment of Cancer (EORTC) Quality-of-Life Questionnaire (QLQ-C30) and its Head and Neck Cancer Module (QLQ-H&N35).Mouth opening or the maximal interincisor opening (MIO) of the mouth, using the Therabite® range of motion scale.Maximum isometric tongue pressure in an anterior position.Maximum inspiratory and expiratory pressures (PImax and PEmax, respectively).Impaired security (tone of voice, coughing during or after eating, or desaturation > 3% compared to baseline pulse oximetry) and efficacy in oral and pharyngeal phases of swallowing with the use of the Volume-Viscosity Swallow Test.Subjective difficulty of swallowing assessed by a Visual Analogic Scale (VAS) ranging from 0 to 10; a low score indicates no difficulties in eating and a high score, no oral intake.Peak cough flow (PCF) will be used to evaluate the effect of IEMT on voluntary cough. It is measured with spirometer in liters/minute. Patients will be instructed to perform three repetitions of voluntary cough and the best one will be chosen.

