#### Statistical methods

Numerical variables will be expressed descriptively as mean and standard deviation (SD). Student *t*-test for paired data will be used to compare the quantitative variables before and after the intervention, and Student *t*-test for independent samples for inter-group comparison of pre- and post-intervention changes. At a later stage, mixed models will be performed to test changes in parameters and the between-group differences in evolution, adjusting by possible confounders. The evaluation of the correlations between variables will be based on the quantitative variables obtained from the various studies and bivariate (ordered Spearman correlation) and multivariate (multiple regression) analysis. Reasons for protocol non-adherence will be registered. The level of alpha risk accepted for all tests will be 0.05.

The evaluation of the correlations between variables will be based on the quantitative variables obtained from the various studies and bivariate (ordered Spearman correlation) and multivariate (multiple regression) analysis. Reasons for protocol non-adherence will be registered and missing data will be discarded. The level of alpha risk accepted for all tests will be 0.05.

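### For the secondary objective of comparing VFSS and V-VST as screens, the only stated analysis that could serve it is correlation and regression, which does not show how many unsafe swallowers the V-VST misses

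*Protocol article*

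**What the plan says.** The objectives at the end of the Background (Protocol article) include "comparing the effectiveness of the VFSS and Volume-Viscosity Swallow Test (V-VST) for screening dysphagia". The Discussion paragraph of the Abstract, which also lists the aims, has no screening comparison. It gives instead the aim "to determine the correlation between a clinical variable and instrumental parameters during this period".

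Under Outcome measures, the V-VST is described by signs: "Impaired security (tone of voice, coughing during or after eating, or desaturation > 3% compared to baseline pulse oximetry) and efficacy" of the oral and pharyngeal phases. No numeric V-VST score is given. For VFSS, the PAS categories are stated: "scores 1–2 indicate normal swallowing, 3–5 penetration, and ≥ 6 aspiration".

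Statistical methods names paired and independent t-tests and then says that "mixed models will be performed to test changes in parameters and the between-group differences in evolution". Relations between variables are to be "based on the quantitative variables obtained from the various studies and bivariate (ordered Spearman correlation) and multivariate (multiple regression) analysis". Sensitivity, specificity, predictive values and agreement are not mentioned.

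**The concern.** Comparing two tests for screening means asking how many patients with impaired swallowing the bedside test detects, how many it misses, and how many it flags wrongly. The t-tests and mixed models address change over time and differences between groups, so they do not bear on this. That leaves the correlation and regression sentence, and the Abstract's wording suggests that correlation is what is meant.

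A correlation measures strength of association and does not separate missed cases from false alarms. Two versions of the V-VST with very different miss rates can produce the same coefficient. An analysis that followed this text could therefore report a moderate correlation and leave a reader unable to tell whether the V-VST is usable as a screen. The sentence is also restricted to quantitative variables, whereas the V-VST is described by signs.

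**Working it through.** **Inputs.** The plan gives no figure for this objective, so there is none to reproduce. Its total of 52 belongs to the between-group comparison. For the PAS difference of 2 (SD 2.3), two-sided 0.05 and 80% power, the normal approximation gives 21 per group; five more for losses makes 26 per group, or 52. Here 52 and 2 × 21 = 42 serve only as plausible numbers of paired assessments. Prevalence, sensitivity and specificity are assumptions; the documents state none of them.

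**Step 1: phi at 30% prevalence.** When both results are coded 0/1, Spearman's rho equals phi. With prevalence p and proportion test-positive q = p·sens + (1 − p)(1 − spec),

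phi = (sens + spec − 1) × √[p(1 − p) / (q(1 − q))].

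- Sens 0.60, spec 0.95: q = 0.180 + 0.035 = 0.215; phi = 0.55 × √(0.210/0.1688) = 0.61. Missed: 40%.
- Sens 0.90, spec 0.77: q = 0.270 + 0.161 = 0.431; phi = 0.67 × √(0.210/0.2452) = 0.62. Missed: 10%.

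**Step 2: other prevalences.** Holding phi at 0.50 and solving for specificity:

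| Prevalence | Spec if sens 0.60 | Spec if sens 0.80 | Spec if sens 0.90 |
|---|---|---|---|
| 30% | 0.88 | 0.74 | 0.65 |
| 50% | 0.88 | 0.70 | 0.57 |
| 70% | 0.94 | 0.72 | 0.57 |

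At each of these prevalences one coefficient is compatible with missing 40% or 10% of cases.

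**Step 3: two whole tables with N = 52, of whom 26 are dysphagic on VFSS.**

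- Table A: 16 true positives, 10 false negatives, 2 false positives, 24 true negatives. Sensitivity 16/26 = 62%, specificity 24/26 = 92%.
- Table B: 24, 2, 10 and 16. Sensitivity 24/26 = 92%, specificity 16/26 = 62%.

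Rho for A is (16×24 − 10×2)/√(26×26×18×34) = 364/643.2 = 0.566. For B it is (24×16 − 2×10)/√(26×26×34×18) = 364/643.2 = 0.566.

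The slope from a linear regression of VFSS status on V-VST status does not separate them either. For A it is 16/18 − 10/34 = 0.889 − 0.294 = 0.595; for B it is 24/34 − 2/18 = 0.706 − 0.111 = 0.595.

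**Step 4: precision of the alternative.** Exact (Clopper-Pearson) 95% intervals for a sensitivity near 85%:

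| N | Prevalence | Detected | 95% CI |
|---|---|---|---|
| 52 | 30% | 14/16 | 62–98% |
| 52 | 50% | 22/26 | 65–96% |
| 52 | 70% | 31/36 | 71–95% |
| 42 | 30% | 11/13 | 55–98% |
| 42 | 50% | 18/21 | 64–97% |
| 42 | 70% | 25/29 | 68–96% |

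**The case against.** The strongest reply is that Statistical methods never assigns correlation to the V-VST objective. The clinical variable in the Abstract is unnamed and could be the visual analogue scale or the EAT-10. If the correlation sentence was never meant for the V-VST, the plan merely leaves one secondary analysis undescribed, which a condensed article may do. This stands to the extent that the link is an inference. The Abstract's list of aims nevertheless has a correlation where the Background has the screening comparison, and no other stated method fits. The text therefore points to an unsuitable method, not only to a missing one.

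Four further points stand. A present/absent V-VST result is a reading of the outcome description, since the scoring is not given. VFSS as reference is also a reading, because the objective names both tests side by side. The PAS describes penetration and aspiration, so it offers no comparator for V-VST efficacy. The illustrations rest on assumed values and on a dichotomised PAS; a rho computed on the full PAS would differ in value, but would still not yield a miss rate.

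A reader might infer that the objective is certain to go unanswered, or that the trial would adopt or reject the V-VST on a correlation. The documents support neither. They set no decision rule for the V-VST, and the cross-tabulation may appear in a fuller plan that is not shown.

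**Conclusion.** The concern holds in a limited form. A secondary objective about screening performance is paired, by the most natural reading of the Abstract and Statistical methods, with an analysis that cannot measure it. That a correlation leaves sensitivity undetermined does not depend on the assumed prevalence: at 30%, 50% and 70%, a coefficient of 0.50 fits sensitivities of both 60% and 90%. The specific pairs shown (0.61 and 0.62 at 30% prevalence; 0.57 for sensitivities of 62% and 92%) are illustrations, not predictions for this trial.

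The conclusion rests on the inferred link and on reading the V-VST security result as present or absent. The randomised comparison, the primary outcome and the sample size are not touched.

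**What to change.** For this objective only, state the following before the V-VST and VFSS results are compared:

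- VFSS is the reference.
- V-VST impaired security (any listed sign present or absent) is cross-tabulated against the PAS at the cut-points implied by the stated categories: 3 or more (penetration or aspiration) and 6 or more (aspiration).
- The visit is fixed in advance, for example t0.
- Sensitivity, specificity and predictive values are reported with exact 95% confidence intervals. If visits are pooled, the intervals allow for clustering within patient.
- The accuracy claim is confined to security, because the PAS gives no comparator for efficacy.

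Spearman correlation can stay for the quantitative measures, such as tongue pressure, respiratory pressures and peak cough flow.

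The cost is a few sentences and one small table. Participant timeline says the study outcomes are assessed at common visits, so new data are probably not needed; the schedule by measure is in Fig. 2, which was not available and should be checked. The intervals will be wide, and the report should say so.

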### Intervention

The training protocol consists of IEMT and standard swallowing exercises. Patients will be instructed to maintain a rate of 15–20 breaths/min using the Orygen-Dual® valve (described elsewhere in detail) [21, 22], a respiratory device that allows patients to train inspiratory and expiratory muscles simultaneously. Training loads will be set at a pressure equivalent to 10 maximal repetitions (if tolerated). These external pressures will be regulated weekly at 30% of maximal inspiration/expiration respiratory measures obtained. Patients will be instructed to perform 3 sets of 5 repetitions and standard swallowing exercises (mobility and tonicity exercises of the tongue, palate, larynx, and constrictor muscles), 3 times/day, 5 days/week, for 21 weeks. An experienced swallowing therapist will supervise IEMT weekly. The protocol will be the same for both groups, but one group will start 2 weeks before CRT and the other one will begin immediately after completing CRT (Fig. 1).

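### The objectives and the cough outcome promise an effect of IEMT, but both arms receive the same IEMT plus standard exercises, so no planned analysis can separate the two components

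*Protocol article*

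**What the plan says.** The Background section gives the main objective as "to determine the effectiveness of 21-week IEMT added to standard swallowing exercises performed before or immediately after CRT", and one of the secondary objectives as "evaluating the effect of IEMT added to standard swallow exercises in a home-based dysphagia rehabilitation program". Under Outcome measures, "Peak cough flow (PCF) will be used to evaluate the effect of IEMT on voluntary cough".

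The Intervention section describes a single package: "The training protocol consists of IEMT and standard swallowing exercises". Both arms get it: "The protocol will be the same for both groups, but one group will start 2 weeks before CRT", and the other group begins once CRT is complete. The Abstract agrees: "All patients will perform the same exercise intervention, but at different times".

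Under Statistical methods, a paired t-test "will be used to compare the quantitative variables before and after the intervention". An independent-samples t-test compares the changes between groups, and mixed models with adjustment for confounders follow later. Under Strengths and limitations, the protocol concedes that there is no control group and defends this by the evidence for swallow and speech therapy.

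**The concern.** An effect of IEMT on top of standard exercises is a difference between patients who have the addition and patients who do not. Here the two components are always given together, so IEMT exposure never varies separately from exercise exposure. The randomised factor is when the package starts.

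The stake is attribution. If early start does better, the result belongs to starting the whole programme early. If peak cough flow or PAS improves within an arm, the change mixes the programme with the course of the disease and its treatment. As the objectives are worded, either result could be reported as evidence for IEMT, and the design supports neither report. A worsening in the early arm could equally be misread as failure of IEMT, although CRT falls inside that arm's training period.

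**Working it through.** **1. The plan's own sample size, and what it is for.** Inputs from Sample size calculation: two-sided alpha 0.05, power 0.80, PAS difference 2 (SD 2.3), quality-of-life difference 10 (SD 11). The normal-approximation formula is n per arm = 2 × (1.96 + 0.84)² × (SD/difference)².

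- PAS: 2 × 7.85 × (2.3/2)² = 20.8, so 21 per arm.
- Quality of life: 2 × 7.85 × (11/10)² = 19.0, so 19 per arm.
- PAS governs: 21 + 5 = 26 per arm, 52 in total.

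The stated 52 reproduces. It is a sample size for one arm against the other, that is, early against late start. At 26 per arm the power is about 0.88 (PAS) and 0.91 (quality of life). None of it applies to IEMT against no IEMT, because the design has no such contrast.

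**2. What each planned analysis compares.**

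| Analysis (Statistical methods) | What differs between the sides | Isolates IEMT? |
|---|---|---|
| Independent t-test of changes | Start time of the whole package | No |
| Mixed models, adjusted | Start time of the whole package, over visits | No; IEMT and standard exercises never vary separately, so adjustment cannot split them |
| Paired t-test within arm | Time, CRT or its aftermath, standard exercises and IEMT together | No |

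**3. What the paired windows contain.** The protocol does not define the before and after visits, so the 21-week programme is taken as the window.

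- Early arm: it starts 2 weeks before CRT, leaving 21 − 2 = 19 weeks after CRT begins. The window covers at least the start of CRT, and all of it if CRT lasts less than 19 weeks (its length is not given). The Background says that CRT impairs swallowing.
- Late arm: it starts at the end of CRT and runs 21 weeks, ending between the 3-month visit (about 13 weeks) and the 6-month visit (about 26 weeks). The Background describes frequent recovery by 3 months and later deterioration through fibrosis.

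Both windows therefore contain change that is expected without any training.

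**4. How easily such change would reach significance.** Assumptions: IEMT does nothing, and the SD of change is 2.3 (the protocol's PAS figure; it does not say that this is an SD of change). The natural mean PAS change m is not given, so a range is shown. The two-sided 0.05 paired t-test has noncentrality m × √n / 2.3. For n = 21 and m = 1 this is 4.58/2.3 = 1.99 on 20 degrees of freedom.

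| Natural mean change m | Significant, n = 21 | Significant, n = 26 |
|---|---|---|
| 0.5 | 16% | 19% |
| 1.0 | 47% | 57% |
| 1.5 | 81% | 89% |
| 2.0 | 97% | 99% |

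**5. What the visits do allow.** Under Participant timeline, t0 is 2 weeks before CRT, t1 its beginning and t3 its end. The late arm starts only after CRT, so at t1 and t3 only the early arm has trained. Early against late at those visits is a randomised comparison of the whole programme with no study exercise. It still cannot separate IEMT from the standard exercises.

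**The case against.** The strongest reply is that the phrase about adding IEMT to standard exercises merely names the package. The Abstract describes the intervention in that way, and on that reading the objective asks about the combined home programme, which the t1 and t3 visits can address. The reading is possible, but the peak cough flow sentence names IEMT alone, and the secondary objective most naturally asks what the addition contributes. If the package is meant, rewording costs nothing.

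The missing control group is also disclosed. However, the defence offered concerns swallow and speech therapy, not IEMT, and the IEMT aim is left standing. The planned mixed models may already include the t1 and t3 contrast. That is a fair point, and it makes the fix cheaper, but the protocol does not single those visits out or say what the contrast would be credited to.

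Some stronger readings are tempting and are not supported:

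- A reader might infer that pre-habilitation is not tested either. It is: start time is randomised, and the between-group analyses address it.
- A reader might infer that the paired t-tests are the planned analysis of the IEMT objective. Statistical methods lists them for quantitative variables in general and does not tie them to that objective.
- A reader might say that the paired changes simply measure toxicity or recovery. They are confounded with both, and may also contain a real programme effect.
- A reader might call the main objective impossible, since only 2 of 21 weeks (about 10%) precede CRT in the early arm. The same sentence equates its wording with early and late intervention, and the Intervention section states the start exactly.

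**Conclusion.** The concern holds as a mismatch between stated aims and design. One secondary objective, the wording of the main objective and the peak cough flow sentence promise an IEMT effect that no planned analysis can identify. This follows from the description of the arms and needs no numerical assumption.

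The paired t-tests cannot stand in for the missing contrast. The 47% and 81% figures (natural change of 1 and 1.5 units) illustrate this and rest on an assumed SD of change of 2.3, 21 completers and no IEMT effect. The documents give no figure for natural PAS change, so these percentages are not a forecast for this trial.

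The randomised comparison of early with late start is valid for the timing question, and the sample size of 52 stands.

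**What to change.** - Restate the objectives in the Background as the effect of starting the combined IEMT and swallowing programme 2 weeks before CRT compared with starting it immediately after CRT.
- Drop the IEMT-specific claim from the secondary objective and the peak cough flow sentence, or reword both to refer to the whole programme.
- Label the within-arm paired t-tests as descriptive.
- Prespecify the between-arm comparison at t1 and t3, adjusted for t0, on PImax, PEmax, peak cough flow and PAS, as the randomised look at the programme against no study exercise. Credit it to the programme, not to IEMT.

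The comparison uses visits at which Participant timeline already places the outcome assessments; the schedule figure is not visible here, so it should be confirmed that each measure is taken at both. Four measures at two visits make 4 × 2 = 8 comparisons, which should be reported as supportive estimates with confidence intervals. Trial status puts the end of data collection in spring 2019, so the change should be dated and fixed before outcomes are examined by arm, or else be labelled post hoc.

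The cost is rewording and one analysis, with no extra patients or visits. The downside is that the trial gives up a claim about IEMT itself, which would need a concurrent arm doing the standard exercises alone.
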